#### Secondary outcome measures

*For clinical practice*: Appropriate call-in of the NST;

*For clinical impact on children*:

Incidence of complications linked to nutritional status during the hospital stay;

Evolution of nutritional status during the hospital stay;

*For economic measures*: Mean length and cost of stay.

Data concerning primary and secondary outcome measures were available at the patient level and were extracted from the medical records by an independent research team. The research team received handouts and training to become familiar with data collection. Data relative to the length of stay and the cost of treatment were obtained from the hospital’s claims databases.

The same data were gathered for the observational study and for the interventional study.

In addition, we monitored the intervention process. The research team gathered information on the availability and usage of the information technology tools, on the actions carried out by the NST in the framework of the awareness campaign for health care workers, and on the actions conducted within the leadership based strategy.

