### Data analysis of the cluster randomised trial

All statistical analyses will be performed in Statistical Analysis System (SAS®) software version 9.2 (SAS Institute, Cary, NC). Analyses will be performed according to the intention-to-treat principle. All malnourished children screened in all clusters allocated to the intervention or control arm will be included in the analysis. In the event of multiple hospitalisations for the same patient, only the first stay of the study period will be retained.

Baseline characteristics will be summarised by pre- and post-intervention period and treatment group using frequency (percentage) for categorical variables and means (standard deviation) for continuous variables.

Clustering will be taken into account: a generalized estimated equations (GEE) approach will be used to analyse the impact of the multifaceted intervention on primary and secondary outcomes [20]. A GEE Poisson regression model will be performed for count data (as number of daily weighings) and GEE logistic regression models for binary variables (as investigation of malnutrition etiology, management by dietician, nutritional supplementation, complication occurrence during hospitalisation). The paediatric departments will be entered as the clustering variable into each model. For the GEE Poisson, the length of stay will be used as an offset. An exchangeable correlation matrix will be specified to account for potential within-cluster homogeneity in outcomes: all pairwise correlations among children within departments are the same. Robust estimates of the standard errors will be obtained which ensures, provided the model is correct, that the estimates are consistent even if the working correlation matrix is not correct. The impact of the multifaceted intervention will be adjusted for individual level characteristics included age, severity of malnutrition, comorbidities occurrence, complications occurrence and length of hospital stay after controlling for the collinearity between covariables. A Wald statistic will be used to test the significance of each coefficient in the model. The intervention effect will be expressed as adjusted odds ratio with its 95% confidence interval. GEE regression models will be fit using the SAS PROC GENMOD. Corresponding overall intra cluster correlation (ICC) coefficient was also estimated from GEE method using the CORRW option from the SAS PROC GENMOD.

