For each arm, comparison of outcome changes between pre- and post-intervention periods will be computed using a GEE regression model, integrating the clustering of children by department. The period following intervention start will be the predictor, while all the potential confounders listed above will be considered in the final model based on a propensity score weighting approach. Immediate change and quarterly trend in clinical practices following the implementation of intervention will be also estimated.

All statistical tests were two-sided with p-value less than 0.05 regarded as significant.

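### The main models adjust the intervention effect for complications and length of stay, two of the trial's own post-randomisation outcomes, so they need not estimate the total intention-to-treat effect

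*Protocol article*

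**What the plan says.** All statements below come from the Protocol article.

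- **Adjustment set.** Under Data analysis of the cluster randomised trial, GEE models are planned for primary and secondary outcomes. The intervention effect is adjusted for age, severity of malnutrition, "comorbidities occurrence, complications occurrence and length of hospital stay after controlling for the collinearity between covariables".
- **The same variables as outcomes.** Secondary outcome measures lists "Incidence of complications linked to nutritional status during the hospital stay" and "Mean length and cost of stay". The data analysis section also names, among the binary dependent variables, "management by dietician, nutritional supplementation, complication occurrence during hospitalisation".
- **Timing.** Under Time frame, the clusters were randomised in February 2010 and trial data run from March 2010 to August 2011.
- **Expected effect.** The Background says that introducing such teams should lower the prevalence of malnutrition-related complications.
- **Weighing outcome.** Outcomes and measurements defines it as total weighings over length of stay. The analysis section adds: "For the GEE Poisson, the length of stay will be used as an offset".
- **Effect measure.** "The intervention effect will be expressed as adjusted odds ratio with its 95% confidence interval".
- **Pre/post comparison within each arm.** For this, "all the potential confounders listed above will be considered in the final model based on a propensity score weighting approach".
- **Principle.** The analysis is declared to be by intention to treat.

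**The concern.** A covariate in the main model of a randomised trial should be one that the allocation cannot have changed. Two of the five listed here do not meet that condition. They are measured during a stay that begins after randomisation, in departments already exposed or not exposed to the intervention, and the trial itself treats them as possible consequences of it.

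Two problems can follow. First, if part of the effect on a care process runs through stay or complications, holding them fixed blocks that part, and the coefficient is no longer the total effect that intention to treat implies. Second, if illness severity that is not captured by the covariates drives complications or stay and also drives care, conditioning on them links allocation to severity and opens a non-causal path.

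The list applies to two of the three primary outcomes through the logistic models and to the third through the Poisson model. The adjusted effect is the only one the article names; no unadjusted or baseline-only model is named for the primary outcomes.

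**Working it through.** **1. The plan's own figure, to see whether it is touched.** Inputs from Sample size calculation and randomisation: 50% against 75%, two-sided alpha 0.05, power 80%, ICC 0.05, cluster size 200.

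- Per arm before clustering: n = [z(0.975)·√(2·0.625·0.375) + z(0.80)·√(0.5·0.5 + 0.75·0.25)]² / 0.25² = 57.7, so 58.
- Design effect: 1 + (200 − 1)·0.05 = 10.95.
- Total: 2 · 58 · 10.95 = 1270, against 1289 stated (1.5% lower, so reproduced).

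No covariate enters this calculation. Changing the adjustment set leaves 1289 as it is.

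**2. Classifying the five covariates.**

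| Covariate | Fixed at admission? | Also an outcome? |
|---|---|---|
| Age | Yes | No |
| Severity of malnutrition | Yes, if the admission value is used | Its change during the stay is |
| Comorbidities | Yes, if limited to pre-existing ones | No |
| Complications | No | Yes, secondary |
| Length of stay | No | Yes, secondary |

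Discussion of study design justifies adjustment by differences in the children's characteristics between clusters. That reason covers the first three rows and not the last two.

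**3. Can adjustment matter, and in which direction?** The documents give no effect on stay or complications, so every value here is an assumption. Individual-level data without clustering were simulated, 400,000 records per scenario, with allocation A and unmeasured severity U:

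- log stay = 2 + 0.3·U + a·A + 0.6·(normal error)
- logit(complication) = −1.7 + 0.6·U + c·A + 0.5·(log stay − 2)
- logit(process outcome) = d·A + u·U + 0.6·(log stay − 2) + 0.5·complication

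The logistic model was fitted with A alone, then with A, log stay and complication.

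| Direct OR, exp(d) | Effect on stay | Complication OR, exp(c) | U affects care (u) | OR, A alone | OR, adjusted for both |
|---|---|---|---|---|---|
| 3 | none | 1 | 0 | 2.86 | 3.01 |
| 3 | −10% | 0.8 | 0 | 2.65 | 3.01 |
| 3 | −20% | 0.6 | 0 | 2.47 | 3.03 |
| 3 | +20% | 0.6 | 0 | 3.06 | 2.96 |
| 1 | −20% | 0.6 | 0 | 0.84 | 0.99 |
| 1 | −20% | 0.6 | 1 | 0.88 | 1.15 |
| 1 | +20% | 0.6 | 1 | 1.06 | 0.92 |
| 1 | none | 1 | 1 | 1.00 | 1.00 |

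Reading the table:

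- Row 1 is non-collapsibility of the odds ratio only, and some of the gap in the next two rows has that source too.
- Row 5 shows the total effect (0.84) replaced by the direct effect (0.99).
- In rows 6 and 7 the adjusted value is neither the total effect (0.88, 1.06) nor the direct effect (1.00), and it lies on the other side of 1 from the total effect.
- Row 8 shows no distortion when the intervention affects neither variable.

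**4. Pre/post comparison.** Period is the predictor and the same list is considered for the weights. In the intervention arm, the post period is when the intervention can change complications and stay. Weighting on them can therefore remove or distort part of the change to be measured.

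**The case against.** The best defence of adjusting for stay is opportunity: a child who stays longer has more time to be seen by a dietician or to have the cause of malnutrition worked up. That is a fair reason for a secondary, labelled model. It does not make stay a baseline variable. For weighings, exposure time is already handled by the offset.

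A second defence is that six clusters make chance imbalance likely. This supports adjusting for characteristics at admission, not for events in hospital. A third is that the article is condensed and that collinearity checks may drop some covariates. But the list is stated, and neither variable is excluded by rule.

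Several stronger readings are tempting and are not supported:

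- *That the primary estimates are biased outright.* Distortion requires the intervention to affect complications or stay. The Background anticipates this for complications. For stay it speaks only of economic savings and does not say that stays will shorten.
- *That the offset is untransformed.* The sentence on the offset is ordinary shorthand, and the outcome defined as weighings over length of stay is the rate that a log offset produces.
- *That complications and stay are covariates in their own models.* One generic list serves all models; the text does not say that an outcome enters its own model.
- *That stay as both offset and covariate is a separate error.* This lets the weighing rate vary with stay; the only objection is that stay is post-randomisation.
- *That the pre/post analysis loses the protection of randomisation.* It is a non-randomised within-arm comparison and never had it. The text also says only that the confounders will be considered.

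**Conclusion.** The point holds in conditional form. The plan adjusts its main intervention effect for two variables that arise after randomisation and that it declares as outcomes. If the intervention changes either one, the result is not the total intention-to-treat effect, and unmeasured severity can add collider bias.

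Size and direction cannot be derived from the documents. The scenarios rest on assumed coefficients and show only that the shift can go either way (0.88 to 1.15, or 1.06 to 0.92) and can be absent (1.00 to 1.00). They are not a forecast for this trial.

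It merits correction before results are reported, because it reaches every primary outcome and an alternative is at hand. The odds-ratio label for the Poisson model is a wording slip, since that sentence fits the logistic models.

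**What to change.** - Delete complications occurrence and length of hospital stay from the covariate list of the main models.
- Keep age, malnutrition severity at admission and pre-existing comorbidity, and state that the latter two are admission values.
- Delete the same two variables from the propensity weights of the pre/post comparison.
- In the weighing model, keep length of stay only as the offset, stated as log length of stay.
- Label any model that also adjusts for complications or stay as exploratory.
- Report a rate ratio for weighings and odds ratios for the binary outcomes.

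The cost is a short edit to the analysis text and a refit of the models. No new data are needed and the sample size is unchanged. The Time frame section says that the statistical work was under way, so the change should be documented with its date and reason.

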### Time frame

The six month observational study was carried out from September 2009 to February 2010. The six clusters were randomised in February 2010. Data from the randomised trial were gathered from March 2010 to August 2011 (18 months). The statistical treatment of these data is currently underway.

Health care workers’ access to the computerised malnutrition screening system was established at the beginning of the intervention study, in the clusters of the intervention arm. The awareness campaign for the health care workers and the leadership based strategy were conducted intensively during the first three months of the intervention study, in the clusters of the intervention arm.

A support phase was conducted throughout the entire intervention period: this included the training of medical residents, the issuing of reminders to the teams regarding the use of the algorithm, and the organisation of department meetings in order to discuss the cases of malnourished children.

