## Discussion

### Discussion of study design

We chose to conduct a cluster randomised trial. This choice is justified with respect to the form of the intervention, which is carried out at the level of the clinical teams (through educational intervention and a computerised malnutrition alert system) and at the level of the dieticians (through a dashboard identifying malnourished children). The intervention was targeted at health care professionals with the aim of studying its impact on patient outcomes [21]. No intervention was performed at the patient level. Data were gathered at the patient level, which means that our analysis had to take two levels into account: the patient level and the cluster level.

Clusters were designed in order to carefully prevent healthcare workers form cross-ward contamination bias. Only a few large sized clusters were available for study (six clusters). This small number of clusters could result in a relatively high probability of chance imbalance between arms. Clusters from our single pool were randomly assigned to the intervention condition or to the control condition. This completely randomised design is most suited to trials in which large numbers of clusters are available for randomisation. We could have opted for a pre-stratification or matching according to baseline characteristics. We will take into account any differences in the characteristics of the children between the clusters within the statistical analysis, by adjusting the models according to the variables of interest.

We performed an observational baseline phase. For six months, prior to the randomised trial, we collected data pertaining to children presenting the inclusion criteria. This phase allowed us to better understand how the treatment of malnourished children was implemented in the departments participating in the study and to test the feasibility of child enrolment. It allowed us to enable calculation of the ICC of the clinical department data (which confirmed that we could retain our hypothesis of an ICC of 0.05). Moreover, it will allow additional statistical analyses comparing main outcome measures before and after implementation of the multifaceted intervention.

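### Baseline outcomes are tested only before versus after within each arm, which does not estimate the intervention effect, and they are left out of the randomised comparison

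*Protocol article*

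**What the plan says.** Under Outcomes and measurements, the Protocol article states that the observational and the trial phase collected the same data. Every randomised cluster therefore has pre-randomisation outcomes.

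The section Data analysis of the cluster randomised trial sets out two analyses.

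- **Between arms.** A GEE model estimates the intervention effect, "adjusted for individual level characteristics included age, severity of malnutrition, comorbidities occurrence, complications occurrence and length of hospital stay". The list contains no baseline-period cluster outcome, no period term and no arm-by-period term.
- **Within arms.** "For each arm, comparison of outcome changes between pre- and post-intervention periods will be computed using a GEE regression model". The model is then defined: "The period following intervention start will be the predictor, while all the potential confounders listed above will be considered in the final model", with propensity score weighting. It adds: "Immediate change and quarterly trend in clinical practices following the implementation of intervention will be also estimated". The closing sentence of the section applies a two-sided 5% significance level to all tests.

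Under Time frame: "The six month observational study was carried out from September 2009 to February 2010". The trial phase then ran from March 2010 to August 2011.

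Under Discussion of study design, the authors accept that six unstratified clusters may well be imbalanced by chance, and propose adjustment for child-level differences as the remedy. On the baseline phase they write that "it will allow additional statistical analyses comparing main outcome measures before and after implementation of the multifaceted intervention". It also served feasibility and an ICC check: "It allowed us to enable calculation of the ICC of the clinical department data".

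**The concern.** There are two linked problems.

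First, a before-after test inside one arm answers whether that arm changed, not whether the intervention changed it. Two such tests side by side, one significant and one not, are not a test of the difference between arms. Here period is also tied to calendar time, and the weighting uses only the patient-level confounders already listed, so it cannot remove a seasonal or secular shift. The quarterly trends have the same weakness: no contrast with control is stated, and the baseline supplies only two quarters.

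Second, the primary outcomes are measures of departmental practice. The imbalance that matters most is therefore how well each cluster already practised before allocation. That was measured, yet the randomised comparison does not use it. Child age, severity or comorbidity cannot stand in for it.

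At stake are the interpretation of the before-after results, and the face validity (possibly the precision) of the main estimate.

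**Working it through.** **1. The plan's own figure.** Inputs from Sample size calculation and randomisation: 50% v 75%, two-sided 5%, power 80%, ICC 0.05, 200 children per cluster.
- Per arm before clustering: (1.960 + 0.842)² × 2 × 0.625 × 0.375 / 0.25² = 58.87.
- Design effect: 1 + 199 × 0.05 = 10.95.
- Total: 2 × 58.87 × 10.95 = 1289.2, which matches the stated 1289. The sample size formula is not at issue here.

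**2. Season.** Months in March to August: 0 of 6 at baseline, 12 of 18 (67%) in the trial. If adherence differs by D between the half-years and intake is even over months, each arm shows a change of D × 12/18 with no intervention effect. D = 5 points gives 3.3 points; D = 10 gives 6.7. D is illustrative; the documents give no seasonal figure.

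**3. Separate tests.** Suppose both arms change by the same 10 points, so there is no intervention effect. Assume three clusters per arm, 200 trial-period and 200 × 6/18 = 67 baseline children per cluster, binary variance 0.25, independent arms, and a normal test with a correct standard error. CAC is the cluster autocorrelation between periods.
- v1 = 0.25 × (0.05 + 0.95/200) = 0.01369
- v0 = 0.25 × (0.05 + 0.95/66.7) = 0.01606
- cov = 0.25 × 0.05 × CAC
- SE of change in one arm = √[(v1 + v0 − 2cov)/3] = 0.076 at CAC 0.5 and 0.057 at 0.8
- Probability p that one arm is significant = 0.26 and 0.42
- Probability that exactly one arm is significant = 2p(1 − p) = 39% and 49%

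**4. Using the baseline in the between-arm estimate.** Same cluster numbers and sizes, binary variance 0.625 × 0.375 = 0.2344, effect 25 points.
- Reliability of a cluster mean: trial period 200 × 0.05/10.95 = 0.913; baseline 0.778.
- Correlation of the two period means: r = CAC × √(0.913 × 0.778).
- Unadjusted SE = √[2 × 0.2344 × (0.05 + 0.95/200)/3] = 0.0925.
- ANCOVA SE = 0.0925 × √(1 − r²), tested on t with 3 df.
- Difference-in-differences (DiD) SE = √[2(v1 + v0 − 2cov)/3], with v1, v0 and cov recalculated at variance 0.2344, on t with 4 df.

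| CAC | r² | ANCOVA SE | ANCOVA power | DiD SE | DiD power |
|---|---|---|---|---|---|
| 0.3 | 0.06 | 0.090 | 48% | 0.118 | 37% |
| 0.5 | 0.18 | 0.084 | 53% | 0.104 | 45% |
| 0.6 | 0.26 | 0.080 | 57% | 0.096 | 51% |
| 0.8 | 0.45 | 0.068 | 69% | 0.078 | 67% |
| 0.9 | 0.58 | 0.060 | 78% | 0.067 | 79% |

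Unadjusted power on t with 4 df is 54%. ANCOVA breaks even at a CAC of about 0.5, DiD at about 0.65.

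**The case against.** **The main inference is randomised.** Both arms are observed over the same 18 months, and the before-after work is labelled additional. This stands. A reader might infer that the trial's conclusion is confounded by season, or that the authors will claim efficacy because one arm changes and the other does not. The text supports neither. The seasonal criticism applies to the within-arm analyses only, and nothing in the documents shows that weighing, work-up or referral does vary by season.

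**The precision gain is conditional.** This also stands. Neither the autocorrelation nor the baseline cluster size is given, and with six clusters the lost degree of freedom can outweigh the gain. One cannot say flatly that the plan discards precision.

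**Few-cluster error rates.** A reader might add that a robust Wald test on three clusters has about 25% type I error: 2 × P(t on 2 df > 1.96 × √(2/3)) = 0.25. That presumes three GEE clusters per arm. The plan enters departments as the clustering variable, and there are eight departments in six clusters. Four per arm gives 19% by the same approximation, and the split between arms is not stated. Small-sample inflation would also affect the between-arm model, so it does not arise from how the baseline is used.

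**The baseline phase has other uses.** It served feasibility, the ICC check and description by period and arm. The point concerns its use in outcome analysis only.

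**A fuller plan may say more.** Possibly, but the article does not merely stay silent: it lists the covariates and specifies the arm-by-arm model.

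**Conclusion.** The point holds in a limited form. The planned within-arm tests and trends do not estimate the intervention effect and are exposed to season and secular trend. That follows from the stated model and calendar and needs no assumed autocorrelation. The size is illustrative: a spurious 3.3 to 6.7 points for a half-year difference of 5 to 10 points, and a 39% to 49% chance of discordant significance when both arms shift equally by 10 points.

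The between-arm model remains a concurrent randomised comparison. Its weakness is that "The impact of the multifaceted intervention will be adjusted for individual level characteristics" alone, which leaves already measured differences in prior practice uncorrected after chance imbalance has been conceded. Whether correcting them also improves power depends on the unknown autocorrelation: a loss of up to about 6 points at 0.3 (48% v 54%), a gain of about 24 points at 0.9 (78% v 54%). These figures assume three clusters per arm, ICC 0.05, and 200 trial and 67 baseline children per cluster. The change is advisable; the point does not invalidate the trial's main analysis.

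**What to change.** 1. Replace the arm-by-arm significance tests with a between-arm contrast of change, and estimate the immediate change and quarterly trends as differences between arms.
2. Report within-arm changes descriptively, without p-values.
3. Adjust the between-arm estimate for each randomised cluster's baseline outcome. Prefer the ANCOVA form to a plain arm-by-period difference-in-differences, which needs a higher autocorrelation to break even. Use small-sample inference based on the randomised clusters.
4. Report the unadjusted trial-period estimate alongside, and fix before analysis which of the two is primary.

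Cost: analysis only, since the data exist and the article describes the statistical work as still in progress. One degree of freedom out of four is lost, and power may fall slightly if cluster practice is unstable between periods.
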